## **10 QUALITY CONTROL AND DATA MANGEMENT**

### **10.1 GOOD CLINICAL PRACTICE**

The study will be conducted along the European directives and ICH Harmonised Tripartite Guideline for good clinical practice E6 (R1 as from June 2017 R2): Note for Guidance on Good Clinical Practice, CPMP/ICH/135/95 Step5.

## **10.2 CALIBRATION AND TRAINING OF INVESTIGATORS**

The Principal Investigators will perform sufficient calibration and training procedures. [name] will calibrate the clinical investigators as to assessment of PI and to the analysis of the video recordings. [name] will supervise the investigator's analysis of the questionnaires. The Department f. Zahn-, Mund- u. Kieferheilkunde, Klinik f. Zahnerhaltungskunde und Parodontologie will provide sufficient opportunities for practising all procedures and will assure good performance.

## **10.3 CASE REPORT FORMS (CRF)**

All of the information collected during the study (PI, questionnaires) will be recorded in the CRF's identified by the volunteer number. The data obtained from video analysis will be directly transferred to electronic files without noting them in the CRF. An example of the CRF is added in the appendix. The Investigators will ensure that the CRFs are properly and completely filled in. Each page must be signed or initialled by the Investigators, signifying agreement with and responsibility for the recorded data. The Investigators have to identify all data that were directly recorded into the CRF (i.e. no prior written or electronic record of data), and to be considered to be source data.

The CRFs will be checked for completeness and plausibility by the Principal Investigators. The Investigators will resolve any queries.

## **10.4 AUDITS AND INSPECTIONS**

The Principle investigators will audit all clinical and assessment procedures in their responsibility on a regular basis. The Investigators and Principle Investigators will make themselves available for each other and will give access to the technical site, the study material, and to volunteer files.

The volunteers' anonymity must be safeguarded and data checked during the audit remain confidential.

## **10.5 DATA MANAGEMENT**

All data collected in the CRFs of this study will be entered into a computer database after termination of the video assessments and will be checked for plausibility. Any discrepancies or errors will be clarified and corrected.

## **11 STATISTICAL METHODS AND DETERMINATION OF SAMPLE SIZE**

### **11.1 STATISTICAL ANALYSIS PLAN**

#### Definition of outcome measures and study objectives

Purpose of the study is to describe quality of current brushing behaviour in adults and thereby to identify needs for further dental education and to associate this with the outcome of the questionnaires to identify predictors for brushing habits.

In a first step the study population will be described with respect to socio-demographic and behavioural characteristics (brushing behaviour). The behavioural characteristics are the following:

- duration of tooth brushing (sec)
- starting location
- type of strokes per sextant
- number of movements between areas
- Toothbrushing systematics

From these data the TSI will be calculated.

In parallel, the information obtained from the questionnaires will be stored in MS-Access-Databases. The scoring of the questionnaires relies on MS-Access-Basic scripts which are already available at the Department of Psychosomatic Medicine and Psychotherapy. The scripts for DKB-35, NEO-FFI and PHQ-D were programmed according to published manuals or articles. These scripts were double checked and debugged. An equivalent procedure will be run for the Dental Anxiety Scale and the Dental Related Self-efficacy. All other forms (e.g. sociodemographic data) do not require standardized scoring procedures. All scores and descriptive data will be exported into a data table, which is compatible with common statistical analysis software (preferably MS-Excel, \*.xlsx).

The primary study aim is to correlate the individual brushing habits (effective brushing duration, frequency of alternations between brushing areas, TSI values) with the single scores and sub-scores obtained from the questionnaires.

Secondary objective is to correlate the brushing performance (PI score) with the effective brushing duration, the frequency of alternations between brushing areas and TSI values.

Furthermore the influence of personal efforts regarding maintenance of oral health (e.g. frequency of visits at the dentist, the frequency of brushing per day) on brushing performance (PI) and brushing systematics (TSI) will be analysed.

The third objective is to correlate the personal efforts regarding maintenance of oral health (e.g. frequency of visits at the dentist, the frequency of brushing per day) with the results of the DKB-35, the Neo-FFI and the PHQ-D.

### Statistical Analysis

For the primary endpoint analysis correlation coefficients for the pairwise correlations between the TSI-score and the single sub-scores obtained from the questionnaires will be computed.

The other endpoints will be analysed descriptively using regression models as appropriate for the respective type of data.

## **11.2 SAMPLE SIZE CALCULATION**

Calculation of sample size are based on own data from a previous study (5) including a comparable population (students without relation to dentistry). From these data a toothbrushing systematics index was developed (TSI, unpublished results). It is intended to use the index as a measure for differences and changes in systematics of participants. A maximum TSI score of 2 can be reached. Non-instructed participants have a mean index score of 1.2 with a MIN of 0.6, a MAX of 1.6 and a SD of 0.3. A difference in TSI score between systematically and non-systematically habitual toothbrushing of 0.15 can be assumed to be clinically relevant. With  $\alpha = 0.05$  and  $\beta = 0.1$  a sample size of 170 can be calculated.

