|                             |                                                                                                                                                                                                                                                                                                                                                                                                                                                                                                                                                                                                                                                                                                                                                                            |                               |
|-----------------------------|----------------------------------------------------------------------------------------------------------------------------------------------------------------------------------------------------------------------------------------------------------------------------------------------------------------------------------------------------------------------------------------------------------------------------------------------------------------------------------------------------------------------------------------------------------------------------------------------------------------------------------------------------------------------------------------------------------------------------------------------------------------------------|-------------------------------|
| ENDPOINTS            | 
First endpoint:
correlation between TSI and sub-scores obtained from the questionnaires
 
Other endpoints:
Correlation between brushing performance (PI score) and the effective brushing duration, the frequency of alternations between brushing areas and TSI values
Analysis of the influence of personal efforts regarding maintenance of oral health (e.g. frequency of visits at the dentist, the frequency of brushing per day) on the brushing performance (PI) und the brushing systematics (TSI)
Correlation between the personal efforts regarding maintenance of oral health (e.g. frequency of visits at the dentist, the frequency of brushing per day) and the results of the DKB-35, the Neo-FFI and the PHQ-D.
 |                               |

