|                             | To be allocated/randomised (if applicable) to trial                                                                                                                                                                                                                                                                                                                                                                                                                                                                                                                                                                                                                                                                                                                        | Not relevant                  |
|                             | To be analysed                                                                                                                                                                                                                                                                                                                                                                                                                                                                                                                                                                                                                                                                                                                                                             | n = 170                       |
| TRIAL DURATION       | Recruitment period (months):                                                                                                                                                                                                                                                                                                                                                                                                                                                                                                                                                                                                                                                                                                                                               | Appr. six month               |

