### **6.4 STUDY POPULATION**

Volunteers to be included are male and female volunteers living in Freiburg and studying at the University in Freiburg with no relation to dentistry and psychology. They will be recruited via advertisements at noticeboards at central points of the University. Group size is 170.

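### The sample size of 170 is justified by a two-group comparison of mean TSI, but the primary analysis is a set of correlations, so the stated power does not describe it

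*Protocol*

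**What the plan says.** Section 11.2 takes its inputs from an earlier study by the same group in comparable students: "Non-instructed participants have a mean index score of 1.2 with a MIN of 0.6, a MAX of 1.6 and a SD of 0.3". It then names the effect of interest: "A difference in TSI score between systematically and non-systematically habitual toothbrushing of 0.15 can be assumed to be clinically relevant". It takes a beta of 0.1 and an alpha of 0.05 and concludes that "a sample size of 170 can be calculated". It does not name the test, its sidedness or the ratio of group sizes.

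Section 6.4 describes one sample: "Group size is 170". The synopsis gives the first endpoint as "correlation between TSI and sub-scores obtained from the questionnaires". The Statistical Analysis part of section 11.1 says that "correlation coefficients for the pairwise correlations between the TSI-score and the single sub-scores obtained from the questionnaires will be computed". The remaining endpoints, there and in the synopsis, are correlations or descriptive regressions. The synopsis has 170 volunteers both assessed for eligibility and analysed.

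**The concern.** A sample size calculation should describe the analysis that it supports. Here it concerns a difference in mean TSI between two kinds of brusher. The protocol neither defines these two kinds, by a TSI cut-off or otherwise, nor compares them in any analysis. For the correlations that form the primary analysis it states no target correlation, no precision and no number of sub-scores.

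At stake is how the results are read. Section 11.1 wants to identify predictors of brushing habits. A reader who takes the 90% from section 11.2 and applies it to a correlation near zero could credit the study with more ability to exclude modest associations than it has.

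**Working it through.** **Inputs.** From section 11.2: difference 0.15, SD 0.3, alpha 0.05, beta 0.1, total 170. Assumed here: two-sided testing, equal groups for the reproduction, the Fisher z approximation for correlations, and complete data on all 170.

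**1. Reproducing 170.** For two means with equal groups:

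n per group = 2 × (1.960 + 1.2816)² × (0.3/0.15)² = 2 × 10.508 × 4 = 84.06, rounded up to 85, so 2 × 85 = 170.

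This matches exactly. Power with 85 per group is 0.903 by the normal approximation and 0.900 by the t distribution. Other readings of the same inputs do not match: a one-sided two-group test needs 69 per group (138 in total), and a two-sided one-sample test needs 43. The two-group reading therefore rests on the wording of section 11.2 and on this match.

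**2. What 170 gives for one correlation.** The standard error of Fisher's z is 1/√(170 − 3) = 1/√167 = 1/12.923.

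- Smallest correlation with 90% power: tanh((1.960 + 1.2816)/12.923) = tanh(0.2508) = 0.246.
- Smallest correlation with 80% power: tanh((1.960 + 0.8416)/12.923) = tanh(0.2168) = 0.213.
- 95% confidence interval at r = 0: ± tanh(1.960/12.923) = ± 0.15. At r = 0.20 it runs from 0.05 to 0.34.

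Power at n = 170 is approximately Φ(atanh(ρ) × 12.923 − 1.960). The number needed for 90% power is ((1.960 + 1.2816)/atanh(ρ))² + 3.

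| True correlation | Power at n = 170 | n for 90% power |
|---|---|---|
| 0.10 | 25% | 1047 |
| 0.15 | 50% | 463 |
| 0.20 | 75% | 259 |
| 0.25 | 91% | 165 |
| 0.30 | 98% | 113 |

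**3. Translating the stated effect into a correlation.** The standardised difference is 0.15/0.3 = 0.5. With equal groups there are two readings of the SD:

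- As the SD within groups: r = 0.5/√(0.5² + 4) = 0.243, with 89% power at n = 170.
- As the SD of the whole sample: r = 0.075/0.3 = 0.25, with 91% power at n = 170.

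**4. Several sub-scores.** The protocol gives no count of sub-scores and plans no adjustment, so this is illustration only. With Bonferroni over an assumed 10 to 20 sub-scores, the correlation detectable with 90% power is 0.306 to 0.321, and power at 0.25 is 69% to 61%.

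**The case against.** The strongest reply is that the number and the power both carry over. Step 3 shows that a standardised difference of 0.5 between equal groups is equivalent to a correlation of about 0.24 to 0.25, for which 170 gives close to 90% power. On this view the protocol lacks only a translation. That stands as a defence of the number. It does not rescue the rationale, because section 11.2 neither makes the translation nor states the equal split on which it depends.

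The second reply is that the study is exploratory. Section 5 says that its purpose is to develop hypotheses, section 6.2 warns that the sample is limited and not representative, and section 11.1 plans to compute coefficients without a significance test or success criterion. No section proposes to conclude that an association is absent, so the risk of misreading lies with the reader and not with a planned claim. This limits the seriousness of the point. It does not remove it, since section 11.2 presents 170 as the result of a calculation with stated alpha and beta, not as a choice based on precision or feasibility.

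**Conclusion.** The point holds as a mismatch between section 11.2 and the primary analysis. The arithmetic behind 170 is right, but the 90% power attaches to a comparison that the study does not make. For one correlation, 170 gives 90% power at about 0.25, 75% at 0.20 and 50% at 0.15, and a 95% interval of about ± 0.15 near zero. These figures assume two-sided 0.05, Fisher z and complete data on 170 volunteers. It should be corrected, but it does not call the study's conduct into question.

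Three stronger readings are tempting and not supported:

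- A reader might infer that 170 is too small. The documents do not show this, because the equivalent correlation has about 89% to 91% power in a single test.
- A reader might infer that the group comparison would be circular, with the groups formed from TSI itself. Section 11.1 lists brushing systematics among the data that feed the TSI, so overlap is plausible, but no section says how the groups would be formed.
- A reader might infer a definite loss of power from multiple testing. That needs a number of sub-scores and an adjustment rule, and the protocol gives neither.

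**What to change.** Keep 170 and replace the rationale in section 11.2:

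- Remove the difference between systematic and non-systematic brushers as the basis of the calculation.
- Lead with precision, which suits an exploratory study: with 170 volunteers the 95% confidence interval for a correlation near zero has a half-width of about 0.15.
- Add the power for one correlation (two-sided 0.05, Fisher z): 90% at about 0.25, 75% at 0.20 and 50% at 0.15. Present 0.25 as what 170 can detect, not as a threshold of relevance, since the protocol gives no argument for one.
- State that no 90% power is claimed across the whole set of sub-scores. If multiplicity is illustrated, label the number of sub-scores as an assumption; for an assumed 10 to 20 with Bonferroni, the correlation detectable with 90% power is about 0.31 to 0.32.

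The cost is one reworded paragraph and the notification to the Ethics Commission that section 12 requires for any protocol change. Recruitment, endpoints, measurements and analysis stay as they are.

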## **12 PROTOCOL AMENDMENTS**

Changes or deviations in the conduct of this protocol will be only permitted after discussion with all persons with responsibilities in the study. The Ethics Commission which granted approval for the study must be notified of all changes in the protocol and must provide written approval if changes are substantial (e.g. change of/within study population, number of participants). In the case that an amendment is made, [name] or [name] will be responsible for notification of the Ethics Commission.

## **13 ETHICS AND REGULATIONS**

### **13.1 ETHICAL CONDUCT OF THE STUDY AND INDEPENDENT ETHICS COMMISSION (IEC) AND RELEVANT AUTHORITIES**

This study is to be conducted in accordance with the ethical principles of the Declaration of Helsinki and according to the principle of Good Clinical Practice. Before starting the study,

the study protocol will be subject of review by the IEC. No volunteer should be admitted to the study before the IEC issues its written approval opinion of the study.

### **13.2 VOLUNTEER INFORMATION AND INFORMED CONSENT**

To all volunteers, the Investigator will explain the kind of trial and the risks involved, and the informed consent will be obtained from and signed by each individual volunteer before screening and inclusion of each individual volunteer. The volunteer will also be informed that she/he is free to withdraw from the trial at any time.

Examples of the volunteer information sheet and the informed consent form are given in the appendix.

### **13.3 VOLUNTEER INSURANCE AND ALLOWANCE**

As no invasive intervention is planned no insurance against injury caused by the procedures related to the study is necessary. The allowance will be 15 Euro per volunteer.

### **13.4 VOLUNTEER DATA PROTECTION AND RETENTION OF STUDY RECORDS**

The study will be performed without recording the volunteer's names, addresses or telephone numbers. All files will be coded by an ID number generated by a random number generator. Other personal data as to social status, age, or gender will be kept under the strict confidence by the Investigator.

The files pertaining to this study will be kept for a period of 10 years from the day of delivery of the final report to the IEC.

A Principal Investigator ([name]) will retain originals of the approved study protocol, copies of completed CRFs, volunteers' participation agreements, relevant source documents and all other supporting documentation related to the study for a period of 10 years. The videos will be backed up on a suitable storage medium. All files must be made available for inspection of all Principal Investigators.

### **13.5 PUBLICATION / PRESENTATION**

The study results will be published, preferably in an indexed journal. Any publication will name either a member of the Department f. Zahn-, Mund- u. Kieferheilkunde, Klinik f. Zahnerhaltungskunde und Parodontologie as first and a member of the Klinik f. Psychosomatische Medizin u. Psychotherapie as last author or vice versa.

